#### Health promoting behaviors

2.7.2

The modified version of the health behavior scale, originally developed to evaluate health-promoting lifestyles,^[10]^ will be used for this study. This self-report scale consists of 25 items related to health responsibility, diet habits, exercise, stress management, and smoking habits. Each item has a 4-point response, from 1 (never) to 4 (always). The higher the score means that the individual more frequently performs healthy behaviors.^[11]^

The motivation scale for healthy behaviors will also be assessed using a self-efficacy questionnaire.^[10]^ The 5 questions therein will be on peoples’ abilities in avoiding greasy food, quitting smoking, exercising regularly, taking necessary medications, relieving mental stress, and obtaining health-related information, and the responses will be provided on a 5-point scale where 1 is Not confident at all to 5 is Absolutely confident.^[12]^

#### QoL

2.7.3

The 12-item short-form health survey (SF-12), and EuroQoL Five Dimensions Questionnaire (EQ-5D) will both be used to assess the participants’ QoL. SF-12 consists of both physical and mental assessing components to evaluate general health status.^[13]^ EQ-5D is composed of the EQ-5D-5L and the EQ visual analog scale (VAS). EQ-5D-5L evaluates mobility, self-care, usual activities, pain/discomfort, and anxiety/depression, while EQ VAS rates a patient's health on a 10-cm vertical line.^[14]^

#### TKM-specific questionnaires

2.7.4

Various TKM-based questionnaires are utilized to evaluate the subhealth status of each participant. The Mibyeong questionnaire is used to evaluate an individual's subhealth status. It assesses 4 physical symptoms (fatigue, pain, low sleep quality, and indigestion) and 3 mental distresses (anxiety, anger, and depression), of which, each item is scored from 1 to 7. An individual is considered as part of the healthy group if they achieve a total score of 26 points or less, while mild subhealth status are those with 27 to 47 points, and, finally, severe subhealth status are people scoring 48 points or more.^[5]^ The Sasang Constitutional type will be judged via a previously validated questionnaire, as well as a specialists’ clinical decision. The questionnaire will collect the usual states of a participant's appetite, digestion, urine and feces, cold/heat sensitivity, etc.^[15]^ Cold/heat sensitivities will also be assessed with a separate, validated questionnaire, as they are integral in figuring out how healthy a person is in terms of TKM.^[16]^

#### Physical and social examination

2.7.5

Investigators will measure a participant's height, weight, vital signs (blood pressure, pulse rate, body temperature), pulse wave, HRV, and body composition (InBody) during every visit. Lifestyle activities, including alcohol-consumption, smoking, exercising, sleeping pattern, and eating habits, will also be investigated at the baseline.

### Hypothesis and sample size calculation

2.8

The primary objective of this study is to compare the awareness levels of subhealth statuses between the MBBG and control groups. The null hypothesis is that there is no difference between the awareness score means between the groups. Since there have not been any previous studies implementing the MBBG application, we adopted another clinical trial to explore the mental health benefits of a mobile application. They addressed a 0.58 effect size with a 6-week test.^[8]^ This study set the intervention period as 12 weeks, and the age for the inclusion criteria is higher, and so we assumed the effect size to be, conservatively, 0.5. Therefore, the sample size has been calculated as 60 per group (2-sided, *α* = 0.05 and 1 − *β* = 0.8, independent *t* test) with G∗ power software version 3.1.3.^[17]^ With a 20% dropout rate expected, we will enroll 150 participants (75 in each group) to account for this.

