### Study design and setting

2.2

This is a prospective, open-label, parallel group, randomized controlled trial. This study will seek to enroll 150 healthy adults, aged from 30 to 49 years, from 2 hospitals (Kyung Hee University Korean Medicine Hospital and Kyung Hee University Korean Medicine Hospital at Gangdong, Seoul) from the Republic of Korea. The study advertisements will be posted online and offline boards. The eligible participants will then be randomly allocated to either the MBBG or control group, at a 1:1 allocation ratio. The MBBG group will then use the application for a total of 12 weeks, while the control group will receive no intervention. All the outcomes will be assessed at the baseline, week 6, and, finally, at week 12. The study procedure is summarized in Figure 1.

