### Statistical analysis

2.9

The full analysis set is defined as a group including participants who are allocated to either the intervention or control group, use the MBBG application at least once, and assesses the primary outcome at least once. Per protocol set is defined as a group of the included participants who follow the trial procedure and demonstrate at least 70% compliance. The study results are analyzed primarily with the full analysis set, and subordinately with the per protocol set.

The primary variable in question is the difference in the subhealth status awareness levels between the baseline (visit 1) and the endpoint (visit 3). The mean difference will be tested using a 2-sample *t* test, or a Wilcoxon rank sum test. Any other continuous variables between the baseline and visits 2 or 3 will be tested independently, by an analysis of covariance with a covariate of the baseline values, while categorical variables will be tested by a Chi-squared or Fisher exact test. Repeated measure analysis of variance will be performed to explore any in-group differences between each of the variables throughout all visits. All of the results, analyzed with R software version 3.5.2 or later, will be addressed at a 95% confidence interval.

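### The stated 60 per group gives about 77.5% power at effect size 0.5, not 80%; the printed inputs require 64 per group

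*Protocol article*

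**What the plan says.** The calculation is in section 2.8 of the protocol article (Hypothesis and sample size calculation). An earlier trial of a mobile application for mental health had reported an effect size of 0.58. The authors reduced this because of the longer intervention and older participants: "so we assumed the effect size to be, conservatively, 0.5". The other inputs are "2-sided, *α* = 0.05", power 0.8, and an "independent *t* test) with G∗ power software version 3.1.3". The result is given as "Therefore, the sample size has been calculated as 60 per group". The next sentence adds the dropout allowance: "With a 20% dropout rate expected, we will enroll 150 participants (75 in each group) to account for this".

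Two other places bear on the check. Section 2.2 (Study design and setting) fixes equal allocation. Section 2.9 (Statistical analysis) states the primary test, applied to the change in awareness score from visit 1 to visit 3: "The mean difference will be tested using a 2-sample *t* test, or a Wilcoxon rank sum test".

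**The concern.** All the inputs to a standard calculation are printed, along with the software and the answer, and the answer does not follow from them. For a two-group t test at effect size 0.5, two-sided 5% and 80% power, the requirement is in the low sixties per group, and 60 lies below it. Sample sizes are rounded up, so ordinary rounding does not explain the difference.

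This figure is the only justification for the trial's size, and it concerns the primary endpoint. If it is wrong, the trial claims a type II error of 20% when its design, at the dropout it plans for, carries one of about 22.5%. The article also calls 0.5 a conservative choice, yet 60 per group gives 80% power only for a somewhat larger effect.

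**Working it through.** **Inputs.** Effect size d = 0.5, two-sided alpha 0.05, power 0.80, independent t test, 20% dropout (all section 2.8); allocation 1:1 (section 2.2).

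**Step 1: try to reproduce 60 per group.** With n per group, the t test has 2n − 2 degrees of freedom and noncentrality d × √(n/2). Power is the probability that a noncentral t variable falls outside the two-sided 5% critical values.

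| n per group | Degrees of freedom | Noncentrality | Critical t | Power |
|---|---|---|---|---|
| 60 | 118 | 0.5 × √30 = 2.739 | 1.980 | 77.5% |
| 63 | 124 | 0.5 × √31.5 = 2.806 | 1.979 | 79.5% |
| 64 | 126 | 0.5 × √32 = 2.828 | 1.979 | 80.1% |
| 75 | 148 | 0.5 × √37.5 = 3.062 | 1.976 | 86.0% |

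Solving for exactly 80% gives n = 63.77, so 64 per group. The plan's 60 is not reproduced.

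**Step 2: normal approximation.** n = 2 × (1.960 + 0.842)² / 0.5² = 2 × 7.851 / 0.25 = 62.8, so 63 per group. By this formula, power at 60 per group is 78.2%. The simpler formula does not give 60 either.

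**Step 3: other readings that might explain 60.**

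- One-sided test at 0.05: 51 per group (t test) or 50 (normal approximation).
- Effect size 0.58, as in the cited trial: 48 per group.
- Wilcoxon test with normal data (relative efficiency 3/π): 63.77 / 0.955 = 66.8, so 67 per group.
- Solving in the other direction, 60 per group gives 80% power when d = 0.516.

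None of the stated or nearby inputs gives 60. An unreported effect size of about 0.516 would.

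**Step 4: the dropout step.** 60 / (1 − 0.20) = 75 per group, 150 in total. This is correct and matches the article, so the shortfall passes unchanged into the enrolment target. Starting from 64, the same step gives 64 / 0.80 = 80 per group, 160 in total.

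**Step 5: what 150 enrolled delivers.** At the planned 20% dropout, 75 × 0.80 = 60 per group remain and power is 77.5%. To keep 64 of 75, dropout must not exceed 1 − 64/75 = 14.7%. With no dropout, power is 86.0%.

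**Step 6: the Wilcoxon option.** If the data were normal, 60 per group would act like 60 × 3/π = 57.3 per group in a t test, with power of about 75.6%. This holds under normality only.

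**The case against.** The arithmetic is not in dispute; the counter-case is about how much it matters.

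- **Size.** The gap is 4 evaluable participants per group. The effect size is itself a judgement borrowed from a different application, and uncertainty about it outweighs the gap. At 60 per group, power would be 88.3% for an effect size of 0.58 and 68.6% for 0.45. This stands. It limits the practical consequence but does not make the printed figure right.
- **Rounding of the input.** The true input may have been about 0.516, printed as 0.5. The article does not show this, and it gives the cited effect to two decimals. The printed figures cannot settle whether the sample size or the effect size was misstated, but they are inconsistent either way. The correction should allow for both possibilities.
- **Dependence on dropout.** The shortfall arises only if dropout exceeds 14.7%. That is true, but the article itself expects 20%, and the stated power should hold at the dropout planned for. The full analysis set in section 2.9 requires only one assessment of the primary outcome, so 60 analysed per group is a planning figure, not a certain one.
- **Wilcoxon.** Section 2.9 does not say when this test would replace the t test. If it is meant for non-normal data, the 3/π efficiency does not apply and the test can have more power than the t test. This stands, so the 75.6% figure is illustrative and the conclusion does not rest on it.

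**Conclusion.** The concern holds. With the inputs printed in section 2.8, the required size is 64 per group by the exact method for the named test, or 63 by the normal approximation. The stated 60 gives 77.5% power, about 2.5 percentage points short, and reaches 80% only at effect size 0.516. Carried through the plan's own dropout step, the difference is 150 against 160 enrolled.

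This rests on the t test named in section 2.8, equal group sizes, and 60 analysed per group at the planned 20% dropout. Type I error, allocation and the analysis method are unaffected, and the trial remains sound at this size. What must be corrected is the statement that justifies it.

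**What to change.** Keep 150 participants and correct section 2.8. State that 60 evaluable participants per group give 77.5% power for an effect size of 0.5 with a two-sided 5% independent t test or, equivalently, 80% power for an effect size of 0.516. If the calculation was run with an unrounded effect size, print that value. It would also help to say that 80% power at 0.5 is retained if dropout is no more than 14.7%.

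If the primary analysis is ever changed to a baseline-adjusted one, restate the power for that analysis with its assumed correlation between baseline and visit 3. The present plan does not require this.

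The cost is a change of wording: the stated power becomes slightly less favourable and recruitment does not change. The alternative, keeping 80% power at 0.5 with 20% dropout, would mean 10 more participants (160).

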### Statistical analysis

2.9

The full analysis set is defined as a group including participants who are allocated to either the intervention or control group, use the MBBG application at least once, and assesses the primary outcome at least once. Per protocol set is defined as a group of the included participants who follow the trial procedure and demonstrate at least 70% compliance. The study results are analyzed primarily with the full analysis set, and subordinately with the per protocol set.

The primary variable in question is the difference in the subhealth status awareness levels between the baseline (visit 1) and the endpoint (visit 3). The mean difference will be tested using a 2-sample *t* test, or a Wilcoxon rank sum test. Any other continuous variables between the baseline and visits 2 or 3 will be tested independently, by an analysis of covariance with a covariate of the baseline values, while categorical variables will be tested by a Chi-squared or Fisher exact test. Repeated measure analysis of variance will be performed to explore any in-group differences between each of the variables throughout all visits. All of the results, analyzed with R software version 3.5.2 or later, will be addressed at a 95% confidence interval.

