### MBBG application for the intervention group

2.5

The Korea Institute of Oriental Medicine, in Daejeon, within the Republic of Korea, has developed MBBG, a mobile application for subhealth management. MBBG aims at assessing a user's subhealth status, as well as their TKM-based health status, which leads it to recommend specific health promoting strategies, such as meditation, exercise, and herbal teas. Patients can check their subhealth status and TKM health information after submitting all of the necessary information, including questionnaire responses. The questionnaires are included within the application, so that the participants in the intervention group can successfully complete these via the application. The examination results (height, weight, vital signs, heart rate variability [HRV], etc) have to be input into the application manually.^[6]^

After their allocation to the intervention group, participants will be educated on how to use the application, verbally, and with a user manual during every visit. They are supposed to use MBBG at least once every day for a total of 12 weeks. The push notification function will be activated to motivate the participant to use the application throughout the study period. The history tracking and user ranking services are also available to help promote the use of MBBG. Participants are not allowed to use any other mobile applications for health management during study participation.

Compliance will be calculated based on how many times participants log onto the application during the 12-week study period. The user satisfaction level will be evaluated via 10 questions at visits 2 and 3, only for participants within the intervention group.

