### No intervention in the control group

2.6

Participants allocated to the control group go through the study without any intervention. They are told to maintain their usual lifestyles during the study period. They are also not supposed to use any other mobile applications for health management.

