#### Subhealth awareness

2.7.1

The primary outcome is the awareness of subhealth status. The participants will be given a questionnaire, consisting of 4 items: “Have you known or heard of subhealth statuses?” “Do you think that preventing diseases is as important as treating them?” “Do you think a professional medical service aimed at managing subhealth statuses is necessary?” “Are you willing to use a professional medical service to manage subhealth status, if available?” Each item is then scored from 1 (Not at all) to 7 (Absolutely), with the total score falling in the range of 4 to 28 points. The higher the score, the higher the awareness level. All participants are supposed to submit the subhealth awareness questionnaire during every visit (visits 1, 2, and 3) either via the mobile application or in a classic face-to-face fashion.

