## Discussion

3

This is a prospective, open-label, parallel group, randomized controlled trial aiming to evaluate the feasibility and effectiveness of a mobile application (MBBG) in managing subhealth statuses of healthy adults. One hundred fifty male or female subjects, without any specific diseases, will be allocated to either the MBBG or no-intervention group, with an allocation ratio of 1:1. Only the participants in the MBBG group will use the application for a total of 12 weeks. The awareness of subhealth status will be the variable primarily assessed, and changes to health promoting behaviors, QoL, TKM-based health questionnaires, and physical examination results will be also be statistically tested.

Mobile applications are a rising instrument aimed at helping people monitor their own health statuses, and in managing their own diseases, such as sleep disorders,^[18]^ diabetes,^[19]^ or even medication adherence.^[20]^ However, their effectiveness has not yet been confirmed.^[7]^ Also, no TKM-based application for health status monitoring, or subhealth management, exist. MBBG is the 1st mobile application, based on TKM theory as well as clinical research, that we expect will be feasible in the primary care for subhealth management.

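### The primary analysis set requires use of the app, which controls never have; as written no control qualifies, and applied to the MBBG arm alone the rule excludes never-users after randomisation

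*Protocol article*

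**What the plan says.** Section 2.9 of the protocol article admits to the full analysis set those "allocated to either the intervention or control group, use the MBBG application at least once, and assesses the primary outcome at least once". The three conditions are joined by a plain conjunction, and the first names both arms. Results are "analyzed primarily with the full analysis set, and subordinately with the per protocol set". The per protocol set consists of "included participants who follow the trial procedure and demonstrate at least 70% compliance".

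Other sections settle who can meet these conditions:

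- Section 2.6: "Participants allocated to the control group go through the study without any intervention".
- Section 3 (Discussion): "Only the participants in the MBBG group will use the application for a total of 12 weeks".
- Section 2.5, on the intervention group: "Compliance will be calculated based on how many times participants log onto the application during the 12-week study period". No compliance measure is given for controls.
- Section 2.4: participants and investigators know the allocation.

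Section 2.9 names no other analysis set, so there is no stated set of all randomised participants.

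**The concern.** One condition for entering the primary set is a behaviour that the design rules out for controls. The definition therefore conflicts with the design, and someone must decide how to read it. The possible repairs are not equivalent: one keeps everyone as allocated, another compares MBBG users with all controls. In an open-label trial that choice should not wait until outcome data can be seen.

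The second repair is the natural one-arm reading, and it has its own difficulty. Whether an MBBG participant ever opens the app is known only after allocation, and controls have no matching exclusion. Two of the four awareness items (section 2.7.1) concern the need for, and willingness to use, a service for managing subhealth. Never opening a subhealth app could plausibly go with those attitudes, so the people removed may not be a random part of the arm.

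**Working it through.** **1. Who can enter the full analysis set, as written**

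| Condition (section 2.9) | MBBG arm | Control arm |
|---|---|---|
| Allocated to an arm | yes | yes |
| App used at least once | possible | no (section 2.6, Discussion) |
| Primary outcome assessed at least once | possible | possible |
| All three met | possible | never |

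Section 2.8 plans 75 per group: 60 / (1 − 0.20) = 75, which reproduces the article's dropout step. Eligible controls are therefore 0 of 75, and a two-sample test has no comparator. The per protocol set gives the same result, because 70% compliance is defined only through log-ons.

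**2. The one-arm reading: formula**

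Let f be the share of the MBBG arm that is excluded, and g the amount, in SD, by which the mean change of those kept exceeds that of those excluded, with no true app effect. The whole-arm mean is (1 − f) × kept mean + f × excluded mean. Hence

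kept mean − whole-arm mean = f × g,

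which is the bias against controls who are all retained. The document gives neither f nor g; all values below are assumptions. The type I error comes from the noncentral t distribution, two-sided at 0.05, with 75 controls.

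**3. Primary set (excluded: never opened the app)**

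| f | MBBG kept | g (SD) | Bias = f × g (SD) | Type I error |
|---|---|---|---|---|
| 5% | 71 | 0.25 to 0.8 | 0.01 to 0.04 | 5.1% to 5.7% |
| 10% | 68 | 0.5 | 0.05 | 6.0% |
| 20% | 60 | 0.25 to 0.8 | 0.05 to 0.16 | 5.9% to 15.1% |

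For the middle row, the noncentrality is 0.05 / √(1/68 + 1/75) = 0.05 / 0.167 = 0.30. The bias of 0.05 SD is 0.05 / 0.5 = 10% of the planned effect size. With 54 MBBG participants against 60 controls, which allows for dropout, the error is 5.8%.

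**4. Per protocol set (excluded: below 70% compliance)**

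With 40% excluded and a gap of 0.3 to 0.5 SD, the bias is 0.40 × 0.3 = 0.12 to 0.40 × 0.5 = 0.20 SD. With 36 (60% of 60) against 60, the type I error is 8.7% to 15.6%. These figures concern the secondary set only.

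**The case against.** The strongest defence is that the intended meaning is clear and the consequence slight. Leaving out people who never start treatment is a familiar convention for a full analysis set. Section 2.5 has MBBG participants trained on the app at every visit, with a manual, push notifications and questionnaires inside the app. A single opening satisfies the rule, so never-users may be close to none. This stands as to size. It does not make the definition correct: the convention is safe when starting cannot depend on known allocation, whereas here allocation is known and the rule can act in one arm only.

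One might also say that controls could open the app, since section 2.7.1 has awareness collected "either via the mobile application or in a classic face-to-face fashion". But section 2.5 ties the in-app questionnaires to the intervention group. If controls could answer that way, their entry to the primary set would depend on the questionnaire route.

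A reader might infer more than the document supports:

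- **That the primary comparison is necessarily no longer randomised, or that its error rate is 9% to 16%.** With few never-users, the set nearly equals the allocated sample. The 9% to 16% belongs to the subordinate per protocol set, under assumed inputs.
- **That the bias must favour MBBG.** The primary variable is change from visit 1 to visit 3. Stable differences in motivation largely cancel in a change score, and on a scale capped at 28 keen users could start high and gain less. The direction is plausible but not shown.
- **That non-uptake is hidden from the feasibility assessment.** Log-ons are measured separately over the 12 weeks, and nothing limits that measure to the full analysis set.
- **That a per protocol set is itself a fault.** Every such set conditions on behaviour after allocation, and this one is already secondary.

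**Conclusion.** The full analysis set is wrong as written. Read literally it contains no controls, and this follows from the document's own statements without any assumption. Read as a rule for the MBBG arm only, it excludes never-users from one arm after open-label randomisation. The resulting bias is probably small: about 0.05 SD and a type I error near 6% if 10% never open the app and the gap is 0.5 SD, less if visit training leaves fewer never-users, and more if either input is larger.

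The case for correction rests on the conflict in the definition of the primary set, not on a large expected distortion. The per protocol definition is a secondary matter of clarity: its compliance rule has no meaning for controls, and under a one-arm reading it compares selected app users with unselected controls.

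**What to change.** In section 2.9, delete the app-use clause. Define the full analysis set as all randomised participants with awareness data, analysed in their allocated group regardless of app use. For the per protocol set, state that the 70% compliance rule applies to the MBBG arm only, and label that comparison as supportive and non-randomised.

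Replacing the per protocol comparison with a complier-average effect, using allocation as the instrument, is not advised. Participants below the 70% cut may still use the app and receive training, so allocation could affect their outcome too. That breaks the exclusion restriction and would overstate the effect if partial use works.

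The cost is a short edit before analysis, with no change to the planned 150 participants. The estimate may be slightly smaller because non-users are kept. The edit does not deal with dropout: never-users who also miss visit 3 would still lack the change score.

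### The primary test uses only the visit 1 to visit 3 awareness change, so full-analysis-set members without visit 3, the week 6 score and baseline adjustment all stay outside the primary comparison

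*Protocol article*

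**What the plan says.** All statements are in the protocol article.

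- **Analysis set (2.9 Statistical analysis).** Beyond allocation, members must "use the MBBG application at least once, and assesses the primary outcome at least once". This set carries the main analysis; the per protocol set is secondary.
- **Primary variable and test (2.9).** "The primary variable in question is the difference in the subhealth status awareness levels between the baseline (visit 1) and the endpoint (visit 3". The groups are compared by a two-sample t test or a Wilcoxon rank sum test, with no covariate.
- **Other variables (2.9).** Other continuous variables, at visit 2 or visit 3, are compared by analysis of covariance with the baseline value as covariate.
- **Within-arm analysis (2.9).** "Repeated measure analysis of variance will be performed to explore any in-group differences between each of the variables throughout all visits".
- **Data collected (2.2 Study design and setting).** "All the outcomes will be assessed at the baseline, week 6, and, finally, at week 12". Section 2.7.1 confirms that the awareness questionnaire is completed at all three visits.
- **Sample size (2.8).** "the sample size has been calculated as 60 per group (2-sided, *α* = 0.05 and 1 − *β* = 0.8, independent *t* test"; then "With a 20% dropout rate expected, we will enroll 150 participants (75 in each group) to account for this".

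**The concern.** The set and the variable do not fit together. Membership needs one awareness score at any visit, whereas the primary variable needs two particular scores. A participant who has used the app and has only a baseline score, or scores at baseline and week 6, can belong to the set and still have nothing to put into the stated test. Unless values are imputed, a result labelled as the full analysis set is then calculated on those who reached visit 3.

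This matters because the arms ask different things of participants. One arm is to use an app at least daily for 12 weeks; the other continues as usual. The trial is open-label and the outcome is self-reported. If people who gain little from the app stop attending, the remaining MBBG participants look better than the randomised group would have. The week 6 score could correct part of this, and it is already collected, but the primary test makes no use of it. The primary test also omits the baseline adjustment that the plan applies to its other continuous variables.

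**Working it through.** **1. The plan's own figures.** Inputs from section 2.8: effect size 0.5, two-sided alpha 0.05, power 0.80, independent t test, 20% dropout.

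- Dropout step: 60 / (1 − 0.20) = 75 per group, 150 in total. This reproduces.
- The 60 per group does not. The normal approximation gives 63 and the exact noncentral t calculation 64; exact power at 60 per group is 0.775. That is a separate point, and nothing below depends on it.
- What matters here is the logic: 75 are enrolled so that 60 remain. The calculation counts dropouts as contributing nothing, which agrees with a test on participants who have visit 3.

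**2. How many have no primary value.** 0.20 × 150 = 30, or 15 per group if dropout is even. This is an upper figure, because some dropouts may fail the app-use condition and fall outside the set.

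**3. Possible bias.** The article gives no dropout rate by arm and no outcome for dropouts, so these are assumptions. If a proportion p drops out of an arm, and the dropouts' mean change is g SD below that of the arm's completers, the completer mean exceeds the full-arm mean by p × g. The bias in the group difference is therefore (p_MBBG − p_control) × g when g is the same in both arms.

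| Dropout MBBG v control | g | Bias in group difference |
|---|---|---|
| 20% v 20% | 0.5 SD | 0 |
| 25% v 15% | 0.5 SD | (0.25 − 0.15) × 0.5 = 0.05 SD |
| 30% v 10% | 0.5 SD | (0.30 − 0.10) × 0.5 = 0.10 SD |

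Equal rates do not protect if the reasons differ. A simulation took about 20% dropout in the MBBG arm, linked to a poor change at visit 2, and outcome-unrelated dropout in control. The correlation between visit 2 and visit 3 changes was set at 0.3 to 0.7. With no true effect, the completers' difference was 0.055 to 0.125 SD under moderate dependence (log-odds of dropout rising by 1 for each SD worse change). It was 0.107 to 0.244 SD if exactly the lowest 20% left. In these scenarios dropout depends on the week 6 score, so an analysis that includes that score can address it, where it was recorded.

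**4. Power gained from week 6.** Let n_c = 60 per group have visit 3, let a share q of the 15 dropouts have a week 6 score, and let r be the correlation of visit 2 and visit 3 changes. For a likelihood analysis,

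variance of the arm mean (in SD² units) = (1 − r²) / n_c + r² / (n_c + 15q), and effective n = 1 / variance.

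- q = 0.25, r = 0.3: 0.91/60 + 0.09/63.75 gives effective n 60.3, power 0.777.
- q = 1, r = 0.7: 0.51/60 + 0.49/75 gives effective n 66.5, power 0.817.

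Against 0.775 at n = 60, the gain runs from 0.2 to 4.2 points. Both q and r are assumed.

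**5. Baseline adjustment.** With equal variances at the two visits and baseline to week 12 correlation ρ, the adjusted analysis has (1 − ρ²) / (2(1 − ρ)) = (1 + ρ)/2 times the residual variance of a change score. That never exceeds 1. The article gives no ρ, so no size is claimed.

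**The case against.** The strongest reply is that the article states no complete-case rule. A full analysis set is normally wider than the completers and is paired with a missing-data rule, which an article may leave to the full protocol or analysis plan. That stands. A reader might infer that the plan prescribes a completers-only analysis, but the text does not say so, and the absence of an imputation rule is not the point here. The point is that the stated primary test uses neither the week 6 score nor the baseline as a covariate.

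Three further inferences are tempting and not supported:

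- **That the set takes in anyone with one awareness score.** It also requires at least one use of the app. Read literally, that condition excludes controls, which is a separate defect in the same sentence.
- **That week 6 awareness is used only within arms.** Because the primary variable is the visit 1 to visit 3 change, week 6 awareness could fall under the other continuous variables and be compared between groups by analysis of covariance. It would still not enter the primary comparison.
- **That the plan infers efficacy from within-arm tests.** The repeated-measures analysis of variance is described as exploratory, and no efficacy claim is attached to it.

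It is also fair that the loss of 30 participants is budgeted in the sample size, that the simplest bias illustration is a tenth of the planned 0.5 SD effect, and that the power gain is modest.

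**Conclusion.** The point holds in this limited form. As stated, the primary test leaves out set members without visit 3 (up to about 30 of 150) unless a document not shown imputes their values. It also leaves out the week 6 score and baseline adjustment.

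The case for change rests on bias more than on power. The bias could be zero, about 0.05 to 0.10 SD under unequal dropout with a common gap, or up to 0.24 SD if the worst responders alone leave the MBBG arm. All of these depend on assumed dropout patterns. The change is worth making because it replaces a stated test with a better one that uses data already being collected; it is not a fatal flaw.

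**What to change.** - **Primary analysis.** Fit a mixed model for repeated measures to awareness at week 6 and week 12, with group, visit, group × visit and baseline awareness. The week 12 group contrast, with its 95% confidence interval, is the primary estimate. Participants lost after week 6 then still contribute.
- **Analysis set.** Define it to match the model. With baseline as a covariate, participants who have only a baseline score add nothing without further assumptions; say so, and state how they are handled. Reword the app-use condition so that it cannot apply to controls.
- **Within-arm analysis.** Keep the in-group repeated-measures analysis of variance descriptive and draw no efficacy conclusion from it. As an illustration of why: with no app effect, an assumed shared drift of 0.2 SD of change and 60 per arm, a paired test is significant in a given arm about 33% of the time, and in the MBBG arm alone about 0.33 × 0.67 = 22% of the time.

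**Cost.** Analysis wording and somewhat more R code, with no new visits or data. The model relies on data being missing at random given group, baseline and week 6. That is weaker than what a completers' test needs, but it cannot be verified from the data.
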